### Statistical analysis

Data will be analyzed using SPSS 24.0 (IBM Corp., Armonk, NY). Each of the cognitive domains assessed will be analyzed separately. From each of the assessments administered, latent variables will be created to represent a global cognitive score for each domain. These variables will be created for both baseline and post-intervention test scores. Given the pilot nature of this study, we will focus on descriptive statistics and calculating effect sizes (Cohen’s d values). Data characteristics permitting (normality, multi-collinearity, sample size), we may conduct additional secondary analyses. For example, a time (baseline, follow up) × group (yoga, aerobic, stretching-toning) repeated measures analyses of covariance controlling for relevant covariates (possible covariates include age, education, stage of cancer, months since diagnosis, attendance, and baseline performance) can be employed to explore intervention effects for each of the cognitive domains. Similar repeated measures analyses could examine intervention effects for cardiovascular fitness and the tertiary psychosocial outcomes. Given that this is a pilot study, no additional subgroup or adjusted analyses are planned. An intent-to-treat analysis approach will be used for any dropouts who completed at least one exercise session. Missing data will be handled using a mean imputation approach. Participants’ exercise session attendance and physical activity performed outside of the session (as reported in home logs) will be factored into analyses as appropriate to control for participants’ adherence to study protocols.

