### Randomization

Participants who are eligible for the study and complete all baseline measurements will be randomly assigned to 1 of the 3 intervention arms using a computer-generated program. Randomization will take place in groups following rounds of advertising and is stratified based on sex, age, and years since cancer diagnosis. Couples or friends who sign up for the study together will be randomized together to avoid contamination across groups. Randomization will take place following completion of all baseline assessments and a week before the 12-week exercise sessions are scheduled to begin. Participants will be notified via a mailed letter and follow-up phone calls confirming their randomized group and logistics (parking and directions) for their 12-week exercise sessions. This is an open label trial with no blinding of participants or assessors.

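### The main result is a Cohen's d with no commitment to baseline adjustment; adjustment stays optional, sex is not among the listed covariates, and jointly allocated couples and friends are not carried into the analysis

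*Protocol article*

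**What the plan says.** All references are to the protocol article.

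- **Main analysis (Statistical analysis).** The focus is stated as: "Given the pilot nature of this study, we will focus on descriptive statistics and calculating effect sizes". The formula for Cohen's d is not given: whether it uses 12-week or change scores, whether it is between or within arms, and which SD divides it. No confidence interval or standard error is mentioned.
- **Baseline scores (Statistical analysis).** Domain scores are built at both times: "These variables will be created for both baseline and post-intervention test scores". The Randomization section requires all baseline measurements to be complete before allocation.
- **Models (Statistical analysis).** Data permitting, "we may conduct additional secondary analyses". The example is a time × group repeated-measures analysis of covariance, for which "possible covariates include age, education, stage of cancer, months since diagnosis, attendance, and baseline performance". The text then says that "no additional subgroup or adjusted analyses are planned".
- **Allocation (Randomization).** It takes place in groups after rounds of advertising and is "stratified based on sex, age, and years since cancer diagnosis". On people who enrol together: "Couples or friends who sign up for the study together will be randomized together to avoid contamination across groups". The Statistical analysis section does not return to these pairs.

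**The concern.** The result that readers and the next trial's designers will take from this study is an effect size from arms of 25. At that size chance differences at baseline are not negligible. Under simple randomization the SE of a baseline difference between two arms is √(2/25) = 0.283 SD, so a gap above 0.3 SD arises with probability 2·[1 − Φ(0.3/0.283)], about 29%. That is close to the lower end of the effect range the article cites (0.32–0.47). The score needed to correct for this is measured in everyone, yet the article gives its use an optional place.

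The analysis also does not follow the allocation in two respects. Sex is used to stratify but is not a listed covariate, and people allocated as a unit are not identified as such. The optional model has a further awkward feature: baseline is one of its two time points and also a possible covariate.

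At stake is the precision and clarity of the estimate. The article's first aim is efficacy, and its Discussion hopes the results will inform a larger efficacy trial.

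**Working it through.** **1. The plan's own figure.** Inputs from the Sample size calculation section: three arms, alpha 0.05/2 = 0.025, power 0.80, f = 0.35, total 75. Power is from the noncentral F distribution.

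- One-way ANOVA on 12-week scores: λ = N·f² = 75 × 0.1225 = 9.19, power 66%; 80% power needs 98 in total. At alpha 0.05 the figures are 76% and 82.
- ANCOVA on one baseline covariate, assumed r = 0.5: λ = N·f²/(1 − r²) = 9.19/0.75 = 12.25, power 0.805; required N = 75.
- Repeated measures, between-arm factor, two time points, assumed r = 0.5: λ = N·f²·2/(1 + r) = 12.25, power 0.806; required N = 75.

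So 75 is matched by calculations that use both time points and not by a comparison of 12-week scores alone. The article names neither the test nor a correlation, so this only suggests that the sample size relies on baseline information.

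**2. Precision of a pairwise difference, 25 per arm.** The baseline to follow-up correlation r is not in the article; the range is assumed. Half-widths are in units of the outcome SD, large-sample, with no dropout:

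- 12-week score only: 1.96·√(2/25) = 0.554 (0.558 when d = 0.32)
- change score: 1.96·√[(2/25)·2(1 − r)]
- ANCOVA: 1.96·√(2/25)·√(1 − r²)

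| r (assumed) | 12-week only | Change score | ANCOVA | ANCOVA v 12-week only | ANCOVA v change |
|---|---|---|---|---|---|
| 0.5 | 0.554 | 0.554 | 0.480 | 13% narrower | 13% narrower |
| 0.7 | 0.554 | 0.429 | 0.396 | 29% narrower | 8% narrower |
| 0.8 | 0.554 | 0.351 | 0.333 | 40% narrower | 5% narrower |

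The last column follows from the ratio √[(1 + r)/2] = 0.866, 0.922, 0.949. Against a 12-week-only d, ANCOVA is worth 25/(1 − r²) = 33, 49 or 69 per arm.

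**3. Stratification factors.** If they explain 5–20% of outcome variance (assumed), the true SE is √(1 − R²) = 0.975 to 0.894 times the naive one. Omitting them makes a naive SE too wide.

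**4. Pairs.** Design effect = 1 + (share in pairs) × ICC. With 20–40% in pairs and ICC 0.2–0.3 (both assumed) it is 1 + 0.2 × 0.2 = 1.04 to 1 + 0.4 × 0.3 = 1.12. The true SE is then √1.04 = 1.02 to √1.12 = 1.06 times the naive one. A nominal 5% test has size 2·[1 − Φ(1.96/√DE)], or 5.5–6.4%. Omitting pairs makes a naive SE too narrow, by a little.

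**5. Baseline as both time point and covariate.** Let B be the baseline and Y the 12-week score, with a time × baseline term in the model.

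- The time × group term is the arm effect on Y − B given B. Subtracting B changes only the coefficient of B, so this equals the ANCOVA arm effect on Y.
- The group main effect is the arm effect on (Y + B)/2 given B. The B part is fully explained by the covariate, so this is exactly half the ANCOVA effect.

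The interaction is therefore sound and the size of the main effect is not.

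**The case against.** **The article does not say baseline is ignored.** This stands. A reader might infer that d is unadjusted, but the text leaves d undefined, builds baseline domain scores and lists baseline performance as a possible covariate. The fault is the missing commitment. The sentence ruling out additional adjusted analyses follows the covariate model, so it excludes adjustment beyond that model; it is not a refusal to adjust.

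**The error bars are not misstated.** This also stands as a limit. No intervals are planned, so error arises only if naive ones are added, and the omissions pull in different directions. Leaving out baseline costs precision but keeps a valid SE, leaving out strata makes it too wide, and leaving out pairs makes it too narrow. That pair members will be treated as independent is an inference from silence.

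**The gain is a best case.** Partly right. The near-doubling of effective sample size at r = 0.7 holds only against a d on 12-week scores. Against change scores the gain is modest.

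**The double use of baseline makes the model uninterpretable, so the covariate should go.** A reader might conclude this, but the algebra does not support it. Dropping baseline would turn the model into a less precise change-score analysis.

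**This is a pilot, and an article may leave detail to a fuller document.** The definition of d could well sit there. But the article itself ranks adjusted modelling as optional, and a descriptive focus on effect sizes is a reason to estimate them well.

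**Conclusion.** The point holds as one about an estimator that is not fixed. The article centres its result on Cohen's d, keeps baseline adjustment optional, omits sex from the listed covariates, and does not carry joint allocation into the analysis. Age and time since diagnosis are already on the list, so the gap in stratification factors is small.

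Baseline is the part that matters. The possible loss runs from about 5% of the interval width (change-score d, r = 0.8) to about 40% (12-week-score d, r = 0.8). It depends on an assumed correlation and on a definition the article does not give. The pair effect is minor unless pairs are common and strongly alike; the article gives neither their number nor their correlation. It is worth changing because the cost is so low, but it does not threaten the validity of the trial.

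**What to change.** - **Main estimate.** For each cognitive domain, fit an ANCOVA of the 12-week score on arm, baseline score, sex, age and years since diagnosis. Add randomization round if there are few rounds.
- **Reporting.** Define d as the adjusted between-arm difference divided by the baseline SD. Give it with a 95% CI for yoga v stretching and toning and for yoga v walking.
- **Pairs.** Record an identifier for people allocated together, and use a cluster-robust SE or a random intercept for the pair.
- **Time × group model.** Let the ANCOVA replace it. If it is kept with baseline as a covariate, include the time × baseline term, interpret only the time × group term, and do not report the group main effect.

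**Cost.** The analysis wording changes, and sign-up pairs must be flagged in the dataset. With 75 participants, three arms leave 72 residual degrees of freedom. Baseline, sex, age and years since diagnosis as single terms bring this to 68, and each round beyond the first takes one more. Participants are asked for nothing new.

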Yoga is a noteworthy exercise modality that should be examined for its improvements in cognitive function and quality of life in clinical populations. As a holistic, mind-body activity, with components centered on meditation, breathing, and postures, it has shown great potential to improve cognitive function [13, 14]. Moreover, it is a low-impact exercise modality that may be more suitable by people limited in their mobility and function. However, little is known about the potential of yoga in maintaining or enhancing cognitive function and/or reducing CRCI among cancer survivors. An evidence-based review of yoga for cancer patients and survivors [15] reviewed 10 yoga-based interventions and noted some positive results, with outcomes primarily focused on psychosocial health and well-being (quality of life, depression, anxiety and stress being the most common). None of the reviewed interventions addressed cognitive function or CRCI.

STAY Fit is designed as a pilot three-arm randomized controlled trial, comparing the benefits of a 12-week yoga and aerobic walking intervention, using a stretching-toning group as an active control. In line with the purpose of conducting pilot studies, we designed this trial to test the feasibility of our methods and procedures for a future large-scale intervention and to explore possible effects and associations as a function of yoga practice on cognitive health [16]. The primary outcomes are measures of cognitive function, specifically domains of executive function, attention, memory, processing speed, and working memory. Secondary outcomes include cardiovascular fitness changes over the course of the intervention. Tertiary measures will examine changes in self-reported quality of life and psychosocial outcomes. Our protocol has been reported here in accordance with the SPIRIT checklist (see Additional file 1).

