### Sample size calculation

We recognize that pilot studies do not typically report formal sample size calculations. However, to aid us in making advertising and recruitment decisions, we ran a very preliminary sample size analysis to get an estimated range of subjects needed. A meta-analysis of yoga effects on cognition [13] indicated an effect size range of .32–.47 (Hedge’s g) favoring the yoga condition. We based our sample size calculations to adequately power for a small effect within this range. Using an alpha of 0.05/2, a power of 0.80, and a conservative estimate of a medium effect size (*f* = 0.35), the desired total sample size is 75 (*N* = 25 per group) for this trial.

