#### Cognitive function (primary outcome)

The primary outcome of the trial is cognitive function. Specifically, we will measure executive function, attention and processing speed, memory, and working memory using the tests presented in Table 1. These measures have been used in the exercise-cognition literature and are partly adapted from the NIH Toolbox. The tasks are computer- and paper-based and will be administered over the two testing sessions on separate days and repeated again after the 12-week intervention. The first testing session consists of immediate and delayed word recall [18], flanker task [19], spatial working memory [20, 21], trail making [22], and matrix reasoning [23] task. The second session consists of relational memory [24], pattern comparison [25], and task switching paradigm [14, 21]. All measures involve a practice phase that explains the task instructions and allows participants to familiarize themselves with the test.

**Table 1 Tab1:** Battery of neurocognitive tests administered at baseline and follow-up

Cognitive test	Cognitive domain	Approximate test duration
Word list (immediate and delayed recall)	Short- and long-term memory	5 min
Flanker task	Attention and inhibitory control	8 min
Spatial working memory	Spatial memory	15 min
Trail making A and B	Visual scanning, mental flexibility, processing speed	5 min
Matrices	Fluid intelligence	10 min
Spatial reconstruction task	Relational memory	Self-paced, 20 trials
Pattern comparison	Processing speed	4 min
Task switching	Mental flexibility	15 min

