## Discussion

### Strengths, limitations, and future considerations

To our knowledge, this is the first pilot randomized controlled trial to examine the effects of yoga on cognition in comparison to aerobic exercise and an active control group. Our use of a comprehensive neurocognitive battery will allow us to examine the global and selective effects of exercise on unique cognitive domains. However, this is a 12-week pilot trial and not without limitations. Although a number of yoga and aerobic exercise studies have demonstrated changes in cognitive function following 8- to 12-week interventions, longer interventions with multiple measurement time points can provide more evidence pertaining to the “dose-response” effect of exercise. The singular follow-up time point will limit us in assessing the maintenance effects for the study outcomes. Due to limited resources, our secondary outcome involves a submaximal fitness test to estimate cardiovascular fitness changes over the course of the intervention. Future studies could employ long-term follow-ups and a graded maximal exercise test that directly assesses peak VO_2_ capacity, which is considered the gold standard for cardiovascular measurement. We hope that our pilot study results will aid in informing a fully powered larger efficacy trial in the future. Results from our trial will also allow researchers to utilize more effective measures, perhaps use of magnetic resonance imaging and monitoring physiological data such as blood biomarkers, to investigate possible underlying mechanisms that mediate the exercise-cognition relationship.

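### Each cognitive domain's main result is an undefined Cohen's d from 25 per arm; a baseline-adjusted between-arm difference with a 95% CI would be more precise at almost no cost

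*Protocol article*

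**What the plan says.** The Statistical analysis section states that, because this is a pilot, "we will focus on descriptive statistics and calculating effect sizes", and names Cohen's d as the effect size. Each domain is analysed on its own, with scores built for baseline and for follow-up. The section does not say how d is formed: between arms at follow-up, between arms on change, or within an arm. A repeated-measures analysis of covariance is given as an example of a secondary analysis that may be run if the data allow, with baseline performance among its possible covariates.

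Under Sample size calculation, "the desired total sample size is 75", which is 25 per arm. That section also cites a meta-analysis of yoga and cognition that "indicated an effect size range of .32–.47" (Hedges' g).

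The domains are grouped in two ways. The Background has five: "specifically domains of executive function, attention, memory, processing speed, and working memory". The section on cognitive function as primary outcome has four: "we will measure executive function, attention and processing speed, memory, and working memory".

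On later use, the section on strengths, limitations and future considerations says "We hope that our pilot study results will aid in informing a fully powered larger efficacy trial in the future". Its limitations cover the length of the intervention, the single follow-up and the submaximal fitness test. The imprecision of the effect estimates is not among them.

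**The concern.** The Background gives the pilot two purposes: testing feasibility for a larger trial and exploring possible effects. For the second, the committed output is d for each domain. That is a weak choice on two counts.

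First, an unadjusted d at this size is very imprecise. The Randomization section requires all baseline measurements to be complete before allocation, so the data needed for a sharper estimate exist for everyone. The plan leaves their use optional.

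Second, several domain values will be reported and neither the outcome section nor the analysis section names a lead domain. The eye goes to the largest, and the largest of several noisy values overstates the effect on average. A reader designing the next trial could take it at face value, and nothing in the Discussion warns against that.

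**Working it through.** **The plan's own figure.** The article gives "Using an alpha of 0.05/2, a power of 0.80" and "a conservative estimate of a medium effect size" (f = 0.35), but names no test. The total of 75 is reproduced by a between-groups test in a three-group, two-time-point repeated-measures design at alpha 0.025, if the correlation between time points is assumed to be 0.5 (power 0.806). A one-way comparison of three groups at alpha 0.025 would need 98. So 75 can be reached, but it does not show how precisely one between-arm d is estimated.

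**Inputs.** From the article: n = 25 per arm, plausible true d of 0.32 to 0.47, four or five domains. Assumed: full follow-up, baseline–follow-up correlation r = 0.5 to 0.7, correlation between domains ρ = 0.3 to 0.5, and the same true effect in every domain.

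**1. Precision of an unadjusted between-arm d.** SE(d) = √(2/25 + d²/100).
- d = 0.32: √(0.08 + 0.00102) = 0.285. The 95% range is 0.32 ± 1.96 × 0.285, or −0.24 to 0.88.
- d = 0.47: √(0.08 + 0.00221) = 0.287. The 95% range is −0.09 to 1.03.

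The half-width is about 0.56. The cited meta-analytic range is only 0.47 − 0.32 = 0.15 wide. (Simulating the small-sample distribution moves the upper limits slightly, to 0.91 and 1.07.)

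**2. The largest of K domain values, true d = 0.32 in all.** The expected maximum is about 0.32 + 0.285 × √(1 − ρ) × m, where m is the mean of the largest of K independent standard normals (1.03 for K = 4, 1.16 for K = 5).

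| K | ρ = 0.3 | ρ = 0.5 |
|---|---|---|
| 4 | 0.56 | 0.53 |
| 5 | 0.60 | 0.55 |

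The overstatement is 0.21 to 0.28, so the four-or-five ambiguity matters little.

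**3. What baseline adjustment buys.** In SD units, the SE of the adjusted follow-up difference is about √((2/25)(1 − r²)).
- r = 0.5: √(0.08 × 0.75) = 0.245, half-width 0.48.
- r = 0.7: √(0.08 × 0.51) = 0.202, half-width 0.40.

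If d were instead based on change scores, the SE in the same units would be √((2/25) × 2(1 − r)): 0.283 at r = 0.5 and 0.219 at r = 0.7. The adjusted difference is more precise in both cases.

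**4. If, and only if, a later trial were sized on such a value.** With two-sided alpha 0.05 and 80% power (assumed), n per arm = 2(2.80/d)², or about 153 at d = 0.32. An observed 0.88 would give about 20. Sizing on the expected largest of four or five values would give about 44 to 57 per arm, with true power of roughly 32% to 40% at d = 0.32.

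**The case against.** The strongest reply is that the harm needs an act the article does not plan. It does not say that the next trial will be sized on the observed d, or that the best-looking domain will go forward. It expresses only a hope of informing a larger trial, and for its own size the team turned to a published meta-analysis rather than a pilot estimate. This stands: step 4 illustrates a misuse and does not describe the plan.

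A reader might also infer that a trial sized on d would be underpowered about half the time because the pilot is small. The figure is right but the cause is not. Any roughly median-unbiased estimate exceeds the truth half the time, whatever the sample size. What 25 per arm determines is the size of the error and of the selection bias.

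Nor does the article show that d will be reported without an interval, or that SDs and retention will go unreported. It commits to descriptive statistics, and a condensed article may leave such details to the full plan. Asking for correlations within classes and within pairs who enrol together would also be unhelpful, since a trial of 75 will contain too few such clusters to estimate them well.

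Lastly, d is undefined, so 0.285 applies to one reading of it. That is fair, but it is itself a reason to state the estimate.

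**Conclusion.** The point holds in a limited form. The plan commits to the less informative summary and leaves the better one optional, although the data for it are already collected. An unadjusted between-arm d carries a 95% margin of about ±0.56, and baseline adjustment would bring it to about ±0.48 to ±0.40 at correlations of 0.5 to 0.7. The largest domain value would average about 0.53 to 0.60 when the truth is 0.32.

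The correlations and the equal true effects are assumptions, because the article gives neither. If domains are more strongly correlated, the selection bias shrinks. If follow-up is incomplete, every margin widens. The documents do not support the claim that the next trial will be underpowered. They support only that the planned focus is a poor basis for planning it, and that the Discussion does not say so. This is a worthwhile change of method and not an error that invalidates the pilot.

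**What to change.** In Statistical analysis, name as the main estimate for each cognitive domain the between-arm difference at follow-up, adjusted for that domain's baseline score, with its 95% CI. It may be standardised, provided the SD used is stated. Report it for every domain, whatever its size.

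In the section on strengths, limitations and future considerations, add that the effect estimates will be imprecise. Caution that the observed d, and above all the largest across domains, should not serve as the planning effect for a larger trial.

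The cost is a few sentences and one simple model per domain, with no extra visits or participants. The downside is that the reported effects will look less definite.

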## Methods

### Study design

The STAY Fit trial is a three-arm randomized clinical exercise trial comparing the effects of a 12-week group-based yoga exercise, aerobic walking, and an active control (stretching and toning) on cognitive function and cardiovascular fitness among adult cancer survivors. We will randomize 75 low active adults between the ages of 30 and 70 years to one of the three conditions. All groups participate in structured group-based exercise led by certified and trained exercise leaders over the course of the 12-week intervention. Study outcomes include cognitive assessments, cardiovascular fitness, and psychosocial questionnaires administered at baseline and following the 12-week intervention.

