### Exercise intervention and active control groups

#### Yoga arm

The yoga intervention consists of two weekly, 90-min group sessions for 12 weeks. The style of yoga selected for the intervention is Hatha yoga, the most popular form of yoga practice in the USA [28] which focuses on practicing physical poses, breathing, and meditation. STAY Fit yoga sessions will be held at a local yoga studio and taught by a certified yoga instructor, who has been instructing and practicing for more than 20 years. Each 90-min session is structured such that participants perform 60-min of stretching and poses (*asana*), 15 min of guided breathing practice (*pranayama*), and 15 min of guided meditation. Table 2 depicts a sample yoga session. Sessions are designed at a beginner level for the first few weeks, with a focus on helping participants develop good form, proper alignment, and postures for the asanas. Props used during the sessions include a yoga mat, chair, blanket, and blocks.

**Table 2 Tab2:** Sequence of Hatha yoga and stretching-toning exercises from week 1 of the STAY Fit Trial

Yoga	Stretching and toning
Poses (*asanas)*	Back arch
*Ardha Matsyendrasana*—twist in simple seated pose	Forward bend
*Marjaryasana/Bitilasana*—cat and cow	Squat
*Tadasana*—mountain pose	Military press
**Utkatasana*—chair pose	Walking dips
*Urdhva Hastasasana*—upward salute	Bicep + fly arm cycle
**Virabhadrasana*—warrior 1 and 2	Wood chop
**Purvottanasana*—intense side stretch	Tricep extension
*Viparita Karani*—Supported legs on the seat of a chair	One leg stand
*Supta Baddha Konasana*—reclining bound angle pose	Side leg abductions
*Supported Savasana*—corpse pose	Bicycle abdominal twist
Breathing (*pranayama*)	
3 parts breath in *Supta Baddha Konasana*	
Mediation	
Guided meditation/body scan while in supported *savasana*	

Note: *Using chair for support

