## Conclusions

In addition to advancing the science of yoga and contributing to the fields of integrative medicine, aging, neurocognition, and cancer survivorship, the results of this proposed randomized control trial could have a significant impact on health care recommendations for cancer survivorship. Our study will determine the efficacy of yoga in improving cognitive health, and if proven effective, the gentle and amenable nature of yoga practice could have far-reaching applications for cancer survivors, many of whom are aging adults who will experience other age-related disabilities, co-morbidities, and overall compromised physical health. If found comparable to or better than aerobic exercise, yoga practice could be recommended and promoted as an alternative form of physical activity for adult cancer survivors to improve cognition and cancer-related cognitive impairment as well as physical and psychosocial health.

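### All arms are delivered in shared exercise classes, but the named analysis and the sample size treat participants as independent, so any test or interval for an arm contrast is too narrow if outcomes correlate within class

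*Protocol article*

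**What the plan says.** Study design describes delivery in all three arms: "All groups participate in structured group-based exercise led by certified and trained exercise leaders". The arm descriptions agree. Yoga is held at one local studio, "taught by a certified yoga instructor, who has been instructing and practicing for more than 20 years", and walking and stretching-toning sessions are run by trained leaders.

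On allocation, the Randomization section says: "Randomization will take place in groups following rounds of advertising and is stratified based on sex, age, and years since cancer diagnosis". It takes place a week before the 12-week sessions begin.

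Statistical analysis gives priority to descriptive statistics and Cohen's d. If the data permit, further secondary analyses may follow, for example "a time (baseline, follow up) × group (yoga, aerobic, stretching-toning) repeated measures analyses of covariance controlling for relevant covariates". The possible covariates are age, education, cancer stage, months since diagnosis, attendance and baseline performance. Class, leader and round are not among them, and the section says that no additional adjusted analyses are planned.

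Sample size calculation arrives at its figure without a design effect: "the desired total sample size is 75 (*N* = 25 per group) for this trial".

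Conclusions states: "Our study will determine the efficacy of yoga in improving cognitive health".

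**The concern.** People in the same arm and round share a leader, a place, a calendar period and each other's company for 12 weeks. If that makes their outcomes alike, the class is a source of variation. Each class belongs to one arm only, so class variation adds directly to the variance of the yoga-versus-walking and yoga-versus-stretching contrasts. An analysis of 75 independent people leaves it out, and an unusually good or poor class can then be read as an effect of the modality.

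This clustering comes from how treatment is delivered. It would remain if nobody enrolled with a companion, so it is separate from the joint allocation of couples and friends.

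At stake are the width of any interval placed around d, the error rate of the optional ANCOVA if it is run, and the planning of the larger efficacy trial that the Discussion says this pilot should inform.

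**Working it through.** **Inputs from the article.** Three arms, 25 per arm, f = 0.35, and "Using an alpha of 0.05/2, a power of 0.80" for sizing. No test level is set for the optional ANCOVA; 5% is used below as the conventional level.

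**Assumptions not in the article.** Class ICC 0.05 (range 0.01–0.10), R = 2 to 5 rounds, one class per arm per round, so m = 25/R people per class.

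**The plan's own figure.** For a one-way three-arm F test with noncentrality N·f² and df 2 and N − 3, f = 0.35 at alpha 0.025 and 80% power needs N = 98. N = 75 gives power 0.66 (0.76 at alpha 0.05). So 75 does not reproduce even under independence. That is a separate matter and does not decide this point.

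**Effect of ignoring class.** With two visits, the time × group test is a one-way F test on change. The design effect is DE = 1 + (m − 1)·ICC. The standard error should grow by √DE, and the effective sample size is 75/DE. For R = 2: m = 12.5, DE = 1 + 11.5 × 0.05 = 1.575, √DE = 1.25, 75/1.575 = 48. False-positive rates come from simulation under the null (40,000 runs per setting). All rows are at ICC 0.05:

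| Rounds | DE | √DE | Effective N | False-positive rate, nominal 5% F test |
|---|---|---|---|---|
| 2 | 1.58 | 1.25 | 48 | 15.0% |
| 3 | 1.37 | 1.17 | 55 | 11.7% |
| 4 | 1.26 | 1.12 | 59 | 9.5% |
| 5 | 1.20 | 1.10 | 63 | 8.0% |

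Over 2–5 rounds, the rate is 5.6–6.7% at ICC 0.01, 6.3–9.0% at ICC 0.02 and 12.1–25.6% at ICC 0.10.

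**Effect of ignoring round.** When the only shared effect is a round effect common to all three arms, leaving it out gives 3.9–5.1% at a nominal 5%. With class 0.05 and round 0.05 together, the rates are 15.0%, 10.7%, 8.6% and 7.6% for 2, 3, 4 and 5 rounds. The inflation therefore comes from class. In a separate simulation with 4 rounds at alpha 0.05, with round variance of 5–20% of the residual variance and arms balanced within round, adding round raised power by about 2–7 points (0.724 to 0.740 at the low end, 0.678 to 0.743 at the high end).

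**Interval for d.** Under independence, the half-width for a two-arm d is about 1.96·√(2/25) = 0.55. Allowing for class, it is q·√(2·DE/25), where q is either 1.96 or the t quantile on 2(R − 1) df. For R = 2: √(2 × 1.575/25) = 0.355, so 1.96 × 0.355 = 0.70 and 4.30 × 0.355 = 1.53. At ICC 0.05:

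| Rounds | Half-width, q = 1.96 | Error df | t quantile | Half-width, t |
|---|---|---|---|---|
| 2 | 0.70 | 2 | 4.30 | 1.53 |
| 3 | 0.65 | 4 | 2.78 | 0.92 |
| 4 | 0.62 | 6 | 2.45 | 0.78 |
| 5 | 0.61 | 8 | 2.31 | 0.71 |

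By the normal approximation, the unadjusted 95% interval covers 1 − 2·Φ(−1.96/√DE), about 88% with 2 rounds and 93% with 5.

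**After allowing for class.** Testing arms against between-class error with round as a block brings the simulated rate back to 4.9–5.1% (2, 3 and 5 rounds). Power at f = 0.35 and alpha 0.05 is then about 0.18, 0.34, 0.45 and 0.52 for 2, 3, 4 and 5 rounds, against 0.76 for the model that assumes independence.

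**The case against.** The strongest reply is that this is a pilot and the ANCOVA is only something that may be done. The plan commits to descriptive statistics and d, and with balanced classes clustering does not bias the point estimate of d. The section sets no test level for the model and mentions no interval. The sizing is described as preliminary and meant to guide recruitment. All of this stands. A reader might infer that a fixed confirmatory 5% test is compromised; the article contains no such test. What remains is that an effect size meant to inform a larger trial is of little use without an honest measure of its uncertainty, and that Conclusions speaks of determining efficacy.

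A reader might also infer that the missing round term narrows the error bars. It does not. Participants in each round are randomised among all three arms, so a round effect cancels from the arm contrast, and omitting it is neutral to slightly conservative. A leak from round into the contrast would need allocation ratios that differ between rounds, which the article does not describe.

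Nor is 8–15% a property of this trial. It depends on an assumed ICC, number of rounds and number of classes per round. An equal ICC in all arms is a further simplification: walking intensity is individualised and participants adjust their own speed and incline, so correlation there may be weaker.

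Finally, the class-level analysis has little power with so few classes. That is true, and it is why it is better used as a sensitivity analysis than as a replacement.

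**Conclusion.** The point holds as a moderate one, conditional on within-class correlation. Delivery is in shared classes, and neither the named analysis nor the sample size allows for it. At class ICC 0.05, with 2–5 rounds and one class per arm per round, a nominal 5% three-arm test would reject falsely about 8–15% of the time; over ICC 0.01–0.10 the range is about 6–26%. At the low end of that range the effect is slight. The direction does not depend on the exact figures: any positive class correlation makes the unadjusted standard error too small.

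The single yoga instructor raises a separate limit. As the Yoga arm section reads, instructor and modality coincide in that arm, and neither a class nor a round term can separate them. The efficacy statement in Conclusions therefore goes further than the design can support.

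**What to change.** In Statistical analysis:

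1. Include randomisation round as a fixed factor in any between-arm model, because allocation is done within rounds. The reason is precision, not error control.
2. Wherever an interval or test accompanies d or the ANCOVA, add a sensitivity analysis that allows for class (arm by round). Use either a random class intercept with Kenward–Roger or Satterthwaite degrees of freedom or, because classes are few, a standard error inflated by √(1 + (m − 1)·ICC) over a stated ICC range such as 0.01–0.10. The class term must act on change or on baseline-adjusted follow-up: in a two-visit layout, an intercept common to both visits cancels from the time × group contrast.
3. Report the class ICC with its interval as an input to the larger trial.

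In Conclusions, limit the yoga statement to this programme as delivered.

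The cost is wording and wider intervals. Class membership should follow from the allocation list and the attendance sheets already kept, so no further participants or procedures are needed. Class-level error has only 2 × (rounds − 1) degrees of freedom, so the class-allowing intervals may be very wide and the ICC imprecise; the article should say so.
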